## Abstract

**Background:**

By end December of 2021, COVID-19 has infected around 276 million individuals and caused over 5 million deaths worldwide. Infection results in dysregulated systemic inflammation, multi-organ dysfunction, and critical illness. Cells of the central nervous system are also affected, triggering an uncontrolled neuroinflammatory response. Low doses of glucocorticoids, administered orally or intravenously, reduce mortality among moderate and severe COVID-19 patients. However, low doses administered by these routes do not reach therapeutic levels in the CNS. In contrast, intranasally administered dexamethasone can result in therapeutic doses in the CNS even at low doses.

**Methods:**

This is an approved open-label, multicenter, randomized controlled trial to compare the effectiveness of intranasal versus intravenous dexamethasone administered in low doses to moderate and severe COVID-19 adult patients. The protocol is conducted in five health institutions in Mexico City. A total of 120 patients will be randomized into two groups (intravenous vs. intranasal) at a 1:1 ratio. Both groups will be treated with the corresponding dexamethasone scheme for 10 days. The primary outcome of the study will be clinical improvement, defined as a statistically significant reduction in the NEWS-2 score of patients with intranasal versus intravenous dexamethasone administration. The secondary outcome will be the reduction in mortality during hospitalization.

**Conclusions:**

This protocol is currently in progress to improve the efficacy of the standard therapeutic dexamethasone regimen for moderate and severe COVID-19 patients.

**Trial registration:**

ClinicalTrials.govNCT04513184. Registered November 12, 2020. Approved by La Comisión Federal para la Protección contra Riesgos Sanitarios (COFEPRIS) with identification number DI/20/407/04/36. People are currently being recruited.

**Graphical abstract:**

[figure not shown]

## Background

So far, the outbreak of COVID-19 has infected around 276 million individuals and caused over 5 million deaths worldwide (https://coronavirus.jhu.edu/map.html), with a current global case-fatality ratio of 2%. The most affected geographic region is the Americas, with a case-fatality ratio of 2.4%.

Several factors predict a poor outcome for COVID-19 patients. These include comorbidities (diabetes, hypertension, obesity) and aging, which are normally accompanied by a dysregulated inflammatory response [1]. Other relevant factors include SARS-CoV-2 neurotropism/neuroinvasive [2–9] as viral RNA was found in the brain of patients who deceased from severe acute respiratory syndrome due to COVID-19 infection [10–12]. Likewise, evidence of astrocytic activation and neuronal damage was reported in severe COVID-19 patients with elevated plasmatic levels of glial fibrillary acidic protein and neurofilament light polypeptide [13]. Other authors have shown extensive infection of astrocytes [14] and neurons in 2D and 3D cultures [15, 16]. The infection of cells of the central nervous system (CNS) results in the expression of pathogen-associated molecular patterns (PAMPs) and danger-associated molecular patterns (DAMPs) that trigger a neuroinflammatory response. The exacerbated systemic inflammation, combined with the consequent breakdown of the blood-brain barrier, induces the migration of cells and peripheral inflammatory mediators into the brain. Together, these factors intensify and sustain neuroinflammation, which, added to peripheral damage, may contribute to multi-organ dysfunction and death [10, 12].

### Natural history of SARS-CoV-2 infection

A clinical staging system for SARS-CoV-2 infection has been proposed. It involves four stages: early infection (Stage I, mild), pulmonary involvement without hypoxia (Stage IIa, moderate), or with hypoxia (Stage IIb), and systemic hyperinflammation (Stage III) [17] (Fig. 1).

**Fig. 1 Fig1:**
[figure not shown]
Inflammatory phenomena associated with SARS-CoV-2 infection and its neurological and respiratory manifestations. The SARS-CoV-2 virus mainly enters the respiratory tract and reaches the lungs through direct ventilation and the CNS through the olfactory and trigeminal nerves. The entry of the virus is facilitated by NRP-1, ACE2 receptors, and protein S activation by TMPRSS2. In the CNS, the virus infects neurons, glial cells, and endothelial cells, increasing the permeability of the BBB. This may cause cerebral edema, intracranial hypertension, and neuroinflammation. If the viral infection continues, the damage spreads throughout the body, causing heart and systemic failure. This damage is associated with increased neuroinflammation directed by microglia and oligodendrocytes, causing damage to the brain stem and dysfunction of the heart and lungs. The exacerbated inflammation and intravascular coagulation induce respiratory arrest, possibly leading to the patient’s death. The inflammation is triggered by viral components (PAMPS) that activate TLR3, 7, and 8 receptors on the cell surface. Consequently, there is an increased production of pro-inflammatory cytokines (TNFα and IL 1β) and ROS, which can modify the P2X7 receptor in the brain and activate the inflammasome by the decrease of K^+.^ The activation of the inflammasome increases the production of IL-6 and pyroptosis. This diagram is based on the knowledge at the time of writing the manuscript

After exposure to SARS-CoV-2, the virus enters the host through the nasal cavity and respiratory airway. Early infection (Stage I) courses with mild and non-specific symptoms (fever, malaise, and asthenia); upon this prodromic phase, the virus binds to its target receptors ACE2, TMPRSS2 [18, 19], and NRP-1, the most recently discovered target [20, 21]. These receptors are highly present in several tissues, including the olfactory neuroepithelium, although to a lesser extent in the sensory olfactory neurons, and the lung [19–22]. Thus, the infection can be established in the lungs (Stage II), leading to viral pneumonia, cough, and fever with or without hypoxia. In the lung, SARS-CoV-2 PAMPs will be recognized by endosomal TLR3, TLR7, and TLR8, and cytosolic RIG-I-like receptors [23]. The virus can also reach the CNS through the olfactory and trigeminal nerve terminals. Once in the CNS, it can infect and damage the endothelium, pericytes, and neural cells that express ACE2 and NRP-1 receptors [20, 21], promoting neuroinflammation (Fig. 1). CNS viral involvement is related to headache, dizziness, and ataxia, but infection also may progress to the whole brain, including the brainstem [5, 6]. In a minority of infected patients, the disease progresses to Stage III, coursing with a hyperinflammatory syndrome. This syndrome is characterized by the sustained production of pro-inflammatory cytokines (including IL-1β and TNFα) and reactive oxygen species (ROS), mitochondrial and lysosomal damage, and the hyperactivation of P2X7 receptors. These processes induce the activation of the inflammasome, which increases IL-6 and leads to pyroptosis. Consequently, the dissemination of viral antigens and RNA into the circulation establishes a persistent inflammatory cycle. Immune complexes can also be generated and deposited in target organs [23–25]. During this phase, sustained neuroinflammation may exacerbate the neuronal injury, spreading damage and contributing to central respiratory failure, ultimately resulting in multi-organ dysfunction [17].

A crucial strategy to treat COVID-19 patients is controlling neural and systemic inflammation. For this purpose, it is essential to consider how viruses invade the human organism. The intranasal route is the most frequent; it allows direct access to both respiratory and central nervous systems through neural pathways [5, 15–18]. Coronaviruses, including SARS-CoV-2, can infect brainstem neurons associated with cardio-respiratory control; thus, pulmonary function is also altered at the central level [5, 26–29]. COVID-19 neurological clinical symptoms, particularly nausea, vomiting, and dysgeusia, seem to involve the dorsal vagal complex (DVC) and the *nucleus tractus solitarius* (NTS), linked to the control of several autonomic functions [26]. The NTS is also a well-known target of neuro-immune activation [30]. Its ascending projections reach the hypothalamic paraventricular nucleus, involved in the activation of the HPA axis, and the rostral ventrolateral medulla (RVM), which controls respiratory and cardiovascular functions [31].

The viral infection in the respiratory and central nervous systems promotes the expression of PAMPs and DAMPs. These signals trigger the inflammasome and oxidative stress [23, 32]. Later during infection, the inflammatory response may become dysregulated, extending the initial damage caused by the infection.

### Adrenal insufficiency in SARS-CoV-2 infection

Critically ill patients affected by different pathologies frequently show adrenal insufficiency, which may increase morbidity and mortality [33, 34]. COVID-19 might affect the hypothalamic-pituitary-adrenal (HPA) axis as well. Hypothalamic and hypophyseal tissues express ACE2 and can therefore be viral targets [35]. The virus may directly damage the hypothalamus and the pituitary, leading to hypothalamic-pituitary dysfunctions.

Since the SARS outbreak of 2003, autopsy studies have demonstrated that coronaviruses affect the HPA axis and promote vasculitis in several organs, including adrenal glands; in particular, adrenal cortical cells undergo degeneration and necrosis [36]. Although the full long-term spectrum of COVID-19 endocrine manifestations is still unclear, several endocrine alterations have been reported in SARS survivors. These include hypocortisolism, hypothyroidism, and low levels of dehydroepiandrosterone, suggesting a transient hypothalamic-pituitary dysfunction [37]. Recently, an Arabian study including 28 patients reported the adrenal response to an acute COVID-19 infection; the median level of morning cortisol was 196 (31–587) nmol/L, and the median level of ACTH was 18.5 (4–38 ng/L). Interestingly, patients with severe disease had lower cortisol and ACTH [38]. In addition, other autopsy studies have found edema, neuronal degeneration, and evidence of viral genome in the hypothalamus [39]. Thus, in the presence of subacute thyroiditis or adrenal insufficiency, corticosteroid therapy should help by reducing high amounts of thyroid hormones and replace adrenal function, improving the evolution of these patients regardless of the route of administration.

### Rationale

Dexamethasone sodium phosphate (ALIN, injectable solution. Chinoin Laboratory) is a highly soluble glucocorticoid with a pH = 7–8.5 that does not harm the nasal mucosa. This synthetic steroid is an anti-inflammatory and immunomodulatory drug that inhibits platelet activation, prostaglandin and leukotriene synthesis, and coagulation by regulating transcriptional factors like NF-κB and AP-1 [40–42]. Furthermore, DXM exerts important neuroprotective effects such as rescuing neurovascular integrity during neuroinflammation [43].

### Dexamethasone: a potent anti-inflammatory drug

Considering that the complications of COVID-19 result from exacerbated peripheral and neural inflammation derived from the so-called cytokine storms, at least three key points have been addressed in the use of DXM for the treatment of Coronavirus patients: timing, dose, and route of administration. First, the drug should not be applied from the beginning of the infection when inflammation favors the control of viral replication and the establishment of an adaptive immune response that serves to control the infection. A low dose of DXM (6 mg per patient for 10 days) has quickly and effectively controlled pulmonary inflammation with minimal negative side effects [44]. In addition, the intranasal route would allow direct access of DXM to the CNS through the olfactory and trigeminus nerves, thereby controlling the sustained neuroinflammation provoked by damage to infected astrocytes, neurons, and microglia. Therefore, cardiac and central respiratory failure could be diminished in COVID-19 patients, avoiding fatalities.

In experimental models, it is well known that drugs administered intranasally usually grant higher bioavailability in the CNS compared with similar doses administered intravenously, since intranasal drugs bypass the BBB and hepatic degradation [45–48]. In addition, intranasal DXM might control inflammation by arriving directly to the respiratory system more effectively and quickly than the intravenous route [46–49]. DXM prevents the binding of ACE2 to the spike protein of SARS-CoV-2 and can also bind to LYS353, an active residue of the receptor-binding domain (RBD) [50]. Moreover, DMX reduces ACE2 expression in several cell types by suppressing type I interferon expression [51]; it can also downregulate neutrophil extracellular traps (NETs), possibly through regulating Toll-like receptors [52]. Hyperinflammation is related to high levels of NETs and neutrophilia, which, in turn, predicts thrombosis and poorer outcomes in acute respiratory distress syndrome (ARDS) [53, 54].

## Methods

### Trial design

The “REVIVAL” trial is an interventional, phase 2, multicenter, open-label, randomized controlled study in adult patients with confirmed COVID-19 diagnosis, designed to evaluate the efficacy (superiority) of low doses of intranasal DXM compared to intravenous administration (allocation ratio 1:1) in patients of five COVID-19 referral centers in Mexico City.

### Eligibility criteria

Inclusion criteria comprise patients of both sexes (non-pregnant female), aged from 18 to 90 years old, with presumptive SARS-CoV-2 infection and more than 5 days of clinical evolution, with moderate to severe symptoms requiring oxygen support or high flux mechanical ventilation (NEWS-2 ≥ 5), and abnormal CT-chest scan CO-RADS > 3. Patients should be diagnosed with atypical pneumonia, confirmed by chest images and oxygen saturation (SpO_2_) lower than 93% in ambient air or a ratio of the partial pressure of oxygen and the fraction of inspired oxygen (PaO_2_: FiO_2_) equal to or lower than 300 mmHg, and a positive RT- PCR SARS-CoV-2 test. These patients will be allocated into the experimental group or the control group in a 1:1 ratio (two arms) (Fig. 2) according to the randomization.

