**Fig. 2 Fig2:**
[figure not shown]
Outline of the REVIVAL trial clinical protocol. Initially, patients will be informed about the clinical trial; if they accept and sign the consent, they will be randomized using the Sealed envelope® software. Group A will receive intranasal DXM; Group B will receive intravenous DXM. Both groups will be sampled on days 0, 3, 6, and 10 post-treatment to collect sera and nasopharyngeal swabs. Patients will be monitored throughout the study. The results will be tested for statistical differences between groups

Exclusion criteria include patients with an RT-PCR SARS-CoV-2 negative test; previously receiving GCs at high doses by oral or intravenous administration; severely immunosuppressed as in AIDS, pregnancy, and autoimmune diseases; those who have received outpatient treatment with steroids for more than 72 h before hospital admission; those older than 90 years; with DXM allergy; risk for glaucoma; or recurrent respiratory diseases. Patients receiving other monoclonal antibody-based treatments such as tocilizumab are also excluded. No other concomitant treatments are prohibited for patient eligibility.

Elimination criteria include voluntary withdrawing, lack of informed consent letter, or imminent risk of death within 48 h.

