#### Sample size and randomization

The analysts of the statistic team calculated the size with EPIDAT version 3.1.2 software, using the option “Sample size and surveillance curves” with an estimated 50% increase in the proportion of patients free of mechanical ventilation [intranasal DXM 70% vs. intravenous DXM 45%]. This value was estimated using the data of the COVID-19 patients registered in Mexican hospitals with a confidence of 95%, power of 80%, and proportion of losses of 10%. A sample size of 60 patients per group was obtained with these parameters. The randomization will be made with Sealed Envelope software. This software is freely available from https://www.sealedenvelope.com/simple-randomiser/v1/lists [Accessed May 5, 2020]. This study is a multicenter randomized controlled trial (Fig. 2).

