#### Statistical analysis

Descriptive statistics using mean (standard deviation) or frequency (percentage) will be used following the dimension scale of the variable. An initial comparison between the hospital will define relevant differences among them. Since healthcare conditions are variable in each hospital included in this study, we will analyze the results with a multilevel mixed longitudinal model. The outcome analysis for NEWS-2 components (i.e., respiration rate, oxygen saturation, systolic blood pressure, pulse rate) will be done using the last observation carried forward (LOCF) in those subjects with at least two observations, this analysis will avoid over-optimistic estimates of efficacy. Other efficacy variables like biochemistry or cell counts will be analyzed without ITT due to the susceptibility to type II error.

Biochemical variables and cell counts will be aggregated using principal component analysis and use the scores if the Kaiser-Meyer-Olkin (KMO) is greater than 0.6 and sphericity *p* < 0.0001. The scores using varimax rotation will be used as dependent variables if the method is suitable for our data. The longitudinal mixed model can be described as:
$$ {y}_{ij}={X}_{ij}\beta +{u}_i+{v}_{j(i)}+{\epsilon}_{ij} $$

where *j* = 1,..,Ti are nested in 10 time points, within *i* = 1,..,5 hospitals. The Xs correspond to fixed variables like the treatments, age, sex, and weight, among other confounders.

A database in vertical format was reshaped to nest the biochemical, inflammatory markers, cell count adjusted by sex, age, and BMI. We will perform restricted maximum likelihood (REML) estimation in case we obtain balanced samples. However, if we obtain an unbalanced sample, we will use maximum likelihood instead [59]. Because we expect a small sample size from some hospitals, we will make inferences using the Kendward-Roger degrees of freedom method. We will make simultaneous inferences about l linear combinations of fixed factors. Despite the complicated situation where *l* > 1 we will consider:
$$ F=\frac{1}{l}{\left(\hat{\beta}-\beta \right)}^T\ L{\left({L}^T\ {\hat{\varphi}}_AL\right)}^{-1}\ {L}^T\ \left(\hat{\beta}-\beta \right) $$

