## Conclusions

Intranasal DXM at low doses could be a more effective therapeutic option to control peripheral and central inflammation during ARDS in severe and critical forms of SARS-CoV-2 infection. In addition, it could stabilize the activity of the HPA axis upon this severe stress condition. Although low-dose systemically administered DXM is beneficial for COVID-19 patients, it cannot reach effective therapeutic concentrations in the CNS to control neuroinflammation. In contrast, intranasal administration of DXM is highly effective in controlling neuroinflammation, as demonstrated in experimental inflammation models [41–44]. Therefore, in the REVIVAL trial clinical protocol, we propose boosting the effect of low-dose DXM treatment through an intranasal route of administration. This route will allow reaching the CNS at therapeutic doses that may effectively reduce the morbidity and mortality in severe or critical COVID-19 patients, further than that reported in the RECOVERY trial.

Low doses of intranasal DXM are currently being tested (clinicaltrials.gov id: NCT04513184) in a randomized study in hospitalized COVID-19 patients (moderate and severe forms). The clinical evolution and respiratory parameters of the patients receiving intranasal DXM (experimental treatment) are compared with those of patients receiving 6 mg of intravenous DXM, the currently recommended treatment (https://www.covid19treatmentguidelines.nih.gov/). Considering the prevalence of metabolic syndrome and obesity in Mexico, the therapeutic scheme has been weight-adjusted. A DXM dose of 0.12 mg/kg is administered for 3 days, followed by a dose of 0.06 mg/kg for 7 days. If the current approach yields fewer adverse effects and does reach the CNS to control neuroinflammation as we hypothesized, there will be direct interest to extend this protocol to several COVID hospitals of the National Health System in Mexico. In addition, increasing the initial sample size (preliminary results) will be required to publish the study and share it with the International scientific community.

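### As worded, patients already on mechanical ventilation can enter, but neither the sample-size basis nor the named model terms say how they are handled

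*Protocol article*

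**What the plan says.** All references are to the protocol article.

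- **Entry.** Eligibility criteria takes patients "with moderate to severe symptoms requiring oxygen support or high flux mechanical ventilation (NEWS-2 ≥ 5" (the bracket closes after the 5).
- **Exclusions.** The list after the Fig. 2 legend has no item on ventilation. The nearest item is in the sentence "Elimination criteria include voluntary withdrawing, lack of informed consent letter, or imminent risk of death within 48 h", which does not remove ventilated patients as a class.
- **Sizing.** Sample size and randomization assumes a "50% increase in the proportion of patients free of mechanical ventilation [intranasal DXM 70% vs. intravenous DXM 45"%. On the source it says: "This value was estimated using the data of the COVID-19 patients registered in Mexican hospitals". It describes neither that cohort's ventilation status at baseline nor how an already ventilated trial patient is to be counted.
- **Outcomes.** The primary outcome is a two-point improvement on the patient's own initial NEWS-2. Secondary outcomes include mortality, time on mechanical ventilation, hospital stay and complications. Freedom from ventilation is not a listed outcome.
- **Analysis.** Statistical analysis refers to "NEWS-2 components (i.e., respiration rate, oxygen saturation, systolic blood pressure, pulse rate". As fixed effects it names treatment, age, sex and weight, and leaves the list open to further confounders.

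**The concern.** The entry phrase joins two different clinical states. One of the five hospitals could read it as high-flow oxygen and another as a ventilator. On its plain words it admits ventilated patients.

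Three things follow.

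1. If free of mechanical ventilation means never ventilated, a patient ventilated at randomisation has already failed the quantity used for sizing. The planned 25-point difference then depends on how many such patients enter, and on whether the 45% and 70% already allow for them.
2. A ventilator can affect respiration rate and oxygen saturation. The documents do not say so; it follows from what a ventilator does. For these patients, part of a NEWS-2 change may reflect support rather than recovery.
3. Ventilation at entry can be expected to predict mortality and time on ventilation strongly (again general knowledge, not a statement in the documents). With 60 per arm, chance alone can leave the arms unequal on it. The ventilation-time outcome would also combine patients ventilated from the start with patients ventilated later.

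**Working it through.** **Inputs.** From Sample size and randomization: 70% vs 45%; "with a confidence of 95%, power of 80%, and proportion of losses of 10"%; 60 per group. The share v ventilated at entry is not given, so 10% to 30% is assumed throughout.

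**Step 1: the plan's own figure.** Two-sided 5% test, 80% power, pooled variance, mean proportion 0.575:

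n = [1.96·√(2·0.575·0.425) + 0.8416·√(0.70·0.30 + 0.45·0.55)]² / 0.25² = (1.370 + 0.569)² / 0.0625 = 60.2, so 61 per arm.

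The unpooled formula gives 58 and the arcsine formula 60. The stated 60 is therefore reproduced as a number before losses. Dividing by 0.90 gives 68, 65 and 67. That gap is a separate matter. Here it means only that 60 randomised leave 54 evaluable per arm, with power

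Φ[(0.25·√54 − 1.370) / 0.676] = Φ(0.690) = 75.5%.

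**Step 2: reading A.** The 70% and 45% hold only in patients not ventilated at entry, and ventilated entrants count as not free in both arms. The overall rates become 0.70(1−v) and 0.45(1−v), and the difference 0.25(1−v).

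| v (assumed) | Overall rates | Difference | Power, 54 per arm | Needed per arm before / after 10% losses |
|---|---|---|---|---|
| 0% | 70% vs 45% | 25 points | 75.5% | 61 / 68 |
| 10% | 63% vs 40.5% | 22.5 points | 65% | 77 / 86 |
| 20% | 56% vs 36% | 20 points | 55% | 97 / 108 |
| 30% | 49% vs 31.5% | 17.5 points | 46% | 123 / 137 |

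**Step 3: reading B.** The registered cohort already contained ventilated patients, and 70% vs 45% describes everyone enrolled. The difference stays at 25 points and the power does not change. If ventilated entrants count as not free and the trial has the same share v, the rates implied for the remaining patients are 0.70/(1−v) and 0.45/(1−v):

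- v = 10%: 78% vs 50%
- v = 20%: 88% vs 56%
- v = 30%: 100% vs 64%

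At 30% every intranasal patient not ventilated at entry would have to stay free of ventilation. Reading B costs no power but is demanding if many ventilated patients enter.

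**Step 4: chance imbalance.** With 60 per arm, the SD of the between-arm difference in the share ventilated at entry is √[2v(1−v)/60]. This is 5.5, 7.3 and 8.4 points for v = 10%, 20% and 30%. The corresponding 95% ranges (±1.96 SD) are about ±11, ±14 and ±16 points.

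**What was not computed.** Steps 2 and 3 concern the sizing quantity only. The documents give no NEWS-2 distribution, so no figure for the primary outcome can be derived.

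**The case against.** A reader might infer that ventilated patients cannot inform the trial's question and should be excluded. The documents do not support that. The question is intranasal against intravenous dexamethasone in moderate and severe COVID-19, judged on NEWS-2 change, with mortality secondary. Ventilated patients contribute directly to mortality, ventilation time, stay and complications. Systolic pressure and pulse are not set by the ventilator, and change is measured from each patient's own starting score. Participants lets a family member consent when the patient cannot sign, which fits enrolling very ill people. Admitting them is a design choice open to the sponsor.

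A reader might also infer that Eligibility criteria and Sample size and randomization contradict each other. They do not in terms. The 45% and 70% are outcome proportions, and the text does not say that the source cohort was unventilated at entry. Under reading B no power is lost.

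Nor does the population shift between sections. Conclusions does hope to "effectively reduce the morbidity and mortality in severe or critical COVID-19 patients", but that looks ahead to what the route may achieve. The same section describes the enrolled patients as moderate and severe, as the Abstract and Participants do.

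Finally, the covariate list is open-ended, and a fuller plan may already include ventilation at entry. That stands: its absence from the article is not an error. What survives is that the article leaves the entry phrase ambiguous and does not say to whom its planning rates apply. Naming this covariate now is also a nearly free improvement.

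**Conclusion.** The concern holds in a limited form. The entry wording permits patients already on mechanical ventilation, nothing excludes them, and the sizing section does not say how they count.

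The planned difference lies between 25 points (reading B, or no ventilated entrants) and 17.5 points (reading A with 30% ventilated). Under reading A, power with 54 evaluable per arm falls from 75.5% to 65%, 55% or 46% at 10%, 20% or 30%. These figures rest on an assumed share, on counting ventilated entrants as not free in both arms, and on an endpoint used for sizing only. They do not measure a loss on NEWS-2.

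For NEWS-2 the supportable statement is qualitative: two of the four named components may be less informative in ventilated patients. The case for adjustment rests on expected prognostic strength and on the chance imbalance possible with 60 per arm. None of this shows that ventilated patients are uninformative or must be kept out.

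**What to change.** 1. **Reconcile the two sections.** In Eligibility criteria, state whether the phrase means high-flow oxygen or a ventilator. In Sample size and randomization, state to whom the 45% and 70% apply and how a patient ventilated at entry counts. Who is to be eligible remains the sponsor's decision.
2. **Adjust.** Add ventilation at baseline (yes/no) as a fixed covariate in the mixed model of Statistical analysis and in the analyses of mortality and ventilation time.
3. **Report.** Keep every randomised patient in the main analysis, and report the primary outcome also in patients not ventilated at entry. This group is defined before treatment, so the randomised comparison within it is preserved.

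Cost: a wording change, one model term and one extra reported analysis. Support at entry is part of the eligibility assessment and clinical data are recorded daily, so no new data collection should be needed. If the phrase turns out to mean high-flow oxygen only and no ventilated patient has entered, items 2 and 3 fall away.
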